### Building and safety-check of individualized PMD

During the intake screening, key information regarding the child's disabilities, needs, handedness, and interests (e.g., color, cartoon/movie character) will be collected. Engineering students from Mechanical, Electrical, and Manufacturing programs will be recruited to participate in the research activities. After CITI certification, these students will modify the PMD under the guidance of an engineering faculty expert (JA, KF). The modifications include customizing the seating and control interface to match the child's physical and cognitive abilities, harness support system (child with or without gastrostomy tube), integrating safety features such as automatic shut-off mechanisms (parental control), and enhancing the device's stability and maneuverability. The ride-on toy will also be modified with a “sit-to-stop” design, in which a power interrupter switch is placed in series with the device's power connection; when pressed down (i.e., when child sits), this switch located under the seat stops the ride-on from moving.

Prior to delivering the PMD to the child, a safety checklist including electrical and mechanical items will be employed. Such items include questions regarding battery modifications, proper wiring (gauge, connections, insulation), rating for switches and other electronic components, structural elements and modifications, harness and support systems, no loose components, no sharp objects, or burrs (cuts, drill holes), and ensuring that the system can operate continuously for 10 min with a 40-pound weight without overheating.

A dedicated time will be allotted for parents/child safety and harness donning training. This type of training will be comparable to previous employed training for the adaptive ride-on program at the University (36). It consists of hand-over-hand guidance to briefly demonstrate to the child the cause-and-effect relationship between the activation interface and toy movement. Simple one-word verbal labels are used in conjunction with the haptic guidance, e.g., Go, Stop, and Push. Following this, the child is given the opportunity for random, free exploration of the motor activation and the consequent movement of the mobility device without further adult instruction. In addition, instruction on how to take care of the device (cleaning, charging) will be presented to parents/guardians.

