### Assessment procedures and outcome measures

The primary aim of this study is to determine whether a full-scale RCT is feasible. The feasibility of a future RCT will be determined using the following progression criteria:
-Recruitment Feasibility: At least 70% of eligible participants consent to enroll within the recruitment period.-Retention Rate: At least 80% of participants complete all study visits and assessments.-Adherence: Participants use the stand-on PMD for an average of at least 20 min per day based on device tracking.-Variability of Primary Outcomes: Standard deviation of biomechanical outcomes should allow for a sample size estimation in a full-scale trial.

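### Minor safety suggestion: the 10-minute loaded heat test is half the length of one unbroken session at the plan's own daily-use threshold

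*Protocol article*

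**What the plan says.** The section on building and safety-checking the device in the Protocol article describes a checklist applied before delivery. One of its items is a functional heat test: "ensuring that the system can operate continuously for 10 min with a 40-pound weight without overheating". The list of items opens with "Such items include questions regarding battery modifications, proper wiring (gauge, connections, insulation), rating for switches and other electronic components", so it is illustrative and may not be complete.

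The same section describes two ways of stopping the device. One is a parent-controlled shut-off. The other is a sit-to-stop design, in which pressing the seat cuts the power: "this switch located under the seat stops the ride-on from moving". Neither is described as responding to temperature or to elapsed running time.

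The section on assessment procedures and outcome measures sets the adherence threshold: "Participants use the stand-on PMD for an average of at least 20 min per day based on device tracking". This is one of a list introduced by "The feasibility of a future RCT will be determined using the following progression criteria". It is therefore a yardstick for judging a future trial and not a dose given to families.

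The section on the intervention protocol and usage tracking sends the device home for three months and encourages use in many places. It states neither a number of sessions nor a maximum session length.

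**The concern.** The plan uses continuous loaded running as its heat test, so the open question is whether 10 minutes is long enough. A child who meets the adherence threshold must have at least one day with 20 minutes of use or more, because an average cannot exceed its largest value. If that day's use is taken without a break, the device runs well past the tested time, and a pass at 10 minutes says nothing direct about the remainder.

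What is at stake is device safety. Each device is individually modified by engineering students under faculty guidance, including changes to the power circuit. It is then used away from the laboratory by children aged 4 to 6 at GMFCS level III, supported by a harness. The statistical side of the trial is not involved.

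**Working it through.** The article gives no figure to reproduce here, so the check compares two stated durations.

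**Inputs from the Protocol article**
- Tested continuous run: 10 min (building and safety-check section).
- Adherence threshold: an average of at least 20 min per day (assessment procedures section).
- Session limit: none stated.
- Planned number of children: ten (participants section).

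**Assumptions, because the article is silent**
- Each use-day consists of one unbroken run.
- The average is exactly 20 min per day over a seven-day week.
- Days of use per week: 7, 5 or 3.

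**Formulas**
- Run length per use-day = 20 × 7 / days used per week.
- Ratio = run length / 10.
- Sessions needed to keep each at 10 min or less = run length / 10, rounded up.
- Largest motor-on share that keeps total running within 10 min = 10 / run length.
- Share of the run covered by a 20 min test = 20 / run length, at most 100%.

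| Use-days per week | Run length (min) | Ratio to tested run | Sessions of ≤10 min needed | Motor-on share giving ≤10 min | Covered by a 20 min test |
|---|---|---|---|---|---|
| 7 | 140/7 = 20.0 | 2.0 | 2 | 50% | 100% |
| 5 | 140/5 = 28.0 | 2.8 | 3 | 36% | 71% |
| 3 | 140/3 = 46.7 | 4.7 | 5 | 21% | 43% |

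Under the one-run assumption, a factor of two is the lower end. The gap closes if use is split as in the fourth column, with cooling between sessions. Total running also stays within 10 min if the motor is on for no more than the share in the fifth column. Those shares only equate running time; they are not overheating thresholds.

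**Extra bench time for ten devices**
- 20 min test: 10 × (20 − 10) = 100 min.
- 30 min test: 10 × (30 − 10) = 200 min.

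**The case against.** The strongest reply is that the two durations measure different things. One is uninterrupted powered running under load. The other is an average of tracked daily use, which the article does not define as motor-on time and does not prescribe to families. The factor of two appears only if a whole day's use is one continuous run, and the article points the other way. Driving is child-activated, and the training includes "random, free exploration of the motor activation and the consequent movement of the mobility device". Sitting down cuts the power, and use is encouraged in several places, which suits short bouts. With two equal sessions a day the ratio falls to 1.0, and continuous running may be harsher than stop-start running of the same total length.

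The article is also a condensed account. The checklist may be fuller than shown, and session guidance may be given to families: "A dedicated time will be allotted for parents/child safety and harness donning training". The wiring, insulation and component-rating checks lower the risk. Finally, 20 minutes has no documented thermal basis either, and it would not cover the longer runs in the table.

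All of this stands as a limit on the point. It rules out calling this a contradiction, a missing item or evidence that a device would overheat, and it makes the 2.8 and 4.7 ratios illustrations only. It does not show that a 10-minute pass covers an unbroken session at the plan's own usage threshold. The suggestion concerns a figure that the article does state, so fuller detail elsewhere reduces its weight without changing that figure.

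**Conclusion.** The point holds as a low-priority suggestion to consider, with medium confidence. The stated heat test does not cover a day's use taken as one unbroken run at the adherence average. The shortfall is a factor of 2.0 with daily use, and 2.8 or 4.7 if the same weekly total falls on five or three days. All three figures depend on the one-run assumption, and the last two also on the assumed days of use. With split sessions or enough motor-off time there is no shortfall in running time.

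**What to change.** In the pre-delivery checklist, lengthen the continuous loaded run from 10 minutes to at least 20 minutes. Keep the present weight and the present pass criterion. No temperature reading needs to be added, and nothing asked of families changes. A 30-minute run is optional and would also cover the 28-minute case, though not the 46.7-minute one.

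The cost is one changed figure and about 100 minutes of bench time for ten devices, or about 200 minutes with the optional longer run. Any device built for a replacement participant adds 10 minutes (20 with the longer run). The one real downside is that a device passing at 10 minutes but failing at 20 would need rework before delivery. That fault is better found on the bench than in use.

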### Intervention protocol and tracking of PMD usage

The intervention period will be three months in which children will take the individually adapted PMD home for use. Figure 1 displays the schedule of enrollment, waitlist period, intervention, and assessments regarding our research activities {13}. Usage is encouraged at home, neighborhood, parks, school, and any other places where the family usually attend. Actual time of device use will be tracked with embedded sensors and stored using local hardware memory devices within the ride-on without any identifier information. No GPS sensors or video/photo/ audio recording devices will be used in any of the mobility devices. The sensor data will be collected during visits by trained CITI-certified study personnel from the home or other location where PMDs may be kept/used. These data will be complemented by parent-report via written log. Bi-weekly follow-up phone calls will be given to maintain rapport with all families.

**Figure 1 F1:**
[figure not shown]
Schedule of participant involvement in research activities.

### Assessment procedures and outcome measures

The primary aim of this study is to determine whether a full-scale RCT is feasible. The feasibility of a future RCT will be determined using the following progression criteria:
-Recruitment Feasibility: At least 70% of eligible participants consent to enroll within the recruitment period.-Retention Rate: At least 80% of participants complete all study visits and assessments.-Adherence: Participants use the stand-on PMD for an average of at least 20 min per day based on device tracking.-Variability of Primary Outcomes: Standard deviation of biomechanical outcomes should allow for a sample size estimation in a full-scale trial.

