#### Secondary (exploratory) objective

To descriptively characterize changes in biomechanical measures related to static balance, dynamic balance, and gait following three months of adapted stand-on PMD use, with the purpose of informing outcome selection and sample-size estimation for future trials.

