#### Secondary (exploratory) outcomes: biomechanical variables

While static balance (37–40) contributes to standing/seating stability and function, the dynamic and reactive components (38–41) are crucial for children to engage in life activities such as navigating through busy school hallways. Secondary, exploratory biomechanical outcome measures organized by assessment task are outlined in Table 1.

**Table 1 T1:** Detail of secondary, biomechanical outcome measures.

Approach	Variable	Level of outcome
Static Balance: NIH Toolbox Standing Balance Test		
Kinetics	• COP sway area (cm^2^) and velocity (m/s) • RMS of COP sway (cm)	• Primary • Primary
Electromyography	• Thigh co-contraction* (Quads:Biceps Fem) • Leg co-contraction (Gastroc:Tibialis Ant) • Peak activity (%movement cycle) of distal vs. proximal muscles	• Secondary • Secondary • Secondary
Dynamic Balance: Five-Times-Sit-to-Stand Test and Modified Timed Up and Go		
Kinematics	• Trunk-pelvis coupling (°) during turning step of mTUG	• Secondary
Kinetics	• Time (ms) to reach peak vGRF (5TSTS) • COP sway area (cm^2^) (5TSTS, mTUG turning step) and velocity (m/s) (5TSTS) • RMS of COP sway (cm) (5TSTS, mTUG turning step)	• Secondary • Primary (5TSTS) • Primary (5TSTS)
Electromyography	• Thigh co-contraction* (Quads:Biceps Fem) • Leg co-contraction (Gastroc:Tibialis Ant)	• Secondary • Secondary
Gait: 10-Meter Walk Test, Self-Selected Speed and Fast Pace		
Kinematics	• Hip posture (°) at terminal stance • Trunk posture (°) at initial contact	• Secondary • Secondary
Electromyography	Peak, mean, and duration (%Gait Cycle) of: • Gastrocnemius, Tibialis anterior • Biceps femoris, Vastus Lateralis • Gluteus Maximus	• Secondary • Secondary • Secondary
Spatiotemporal Characteristics	• Speed (m/s) • Single limb stance time (%Gait Cycle)	• Secondary • Secondary

5TSTS, five-times-sit-to-stand test; COP, center of pressure; Gastroc:Tibialis Ant, ratio of gastrocnemius to tibialis anterior; mTUG, modified timed up and go; Quads:Biceps Fem, ratio of quadriceps femoris to biceps femoris; RMS, root mean square; vGRF, vertical ground reaction force.

* Unitless.

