### Statistical treatment

Due to the pilot nature of this study, descriptive statistics will be used to summarize feasibility outcomes, including recruitment, adherence, and retention rates. Variability in biomechanical measures will be estimated using means, standard deviations, and confidence intervals to guide sample size calculations for a future RCT. Given the small sample size, formal hypothesis testing will not be conducted. Preliminary pre-post comparisons of biomechanical outcomes will be reported using effect sizes (e.g., Cohen's d) and confidence intervals. Statistical analyzes will be performed with IBM SPSS Statistics version 28.0 (IBM Co., Armonk, NY, USA).

An external biostatistician will be contracted to perform all statistical treatments and control for any potential observer bias. The biostatistician will also manage the dataset to adjust for any missing data. We envision the use of multiple imputation where necessary, with assumption that the mechanism of missing data points was missed at random.

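### The variability progression criterion sets no limit on an acceptable SD and does not say clearly which outcomes it covers, while an SD from ten children is too imprecise to size an RCT without a rule for its uncertainty

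*Protocol article*

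**What the plan says.** The Primary objective section of the protocol article lists four things to assess: recruitment, retention, adherence and variability in key outcome measures. Under Assessment procedures and outcome measures, each becomes a decision rule: "The feasibility of a future RCT will be determined using the following progression criteria". The rules are:

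- Recruitment: "At least 70% of eligible participants consent to enroll within the recruitment period".
- Retention: "At least 80% of participants complete all study visits and assessments".
- Adherence: "Participants use the stand-on PMD for an average of at least 20 min per day based on device tracking".
- Variability, under a label that refers to primary outcomes: "Standard deviation of biomechanical outcomes should allow for a sample size estimation in a full-scale trial".

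The next subsection classes the biomechanical measures differently: "Secondary, exploratory biomechanical outcome measures organized by assessment task are outlined in Table 1". The Secondary (exploratory) objective does the same and gives their purpose as "with the purpose of informing outcome selection and sample-size estimation for future trials". Table 1, whose title calls its contents secondary, nonetheless has a column that grades some variables Primary.

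Statistical treatment adds: "Variability in biomechanical measures will be estimated using means, standard deviations, and confidence intervals to guide sample size calculations for a future RCT". The sample is ten children in a single arm.

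**The concern.** A progression criterion is useful only if some plausible result would fail it. Three of these rules meet that test. The fourth asks only that an SD permit a sample-size calculation, and any finite, non-zero SD does. A very large SD, implying an RCT that could never be recruited, would pass just as a small one would. One of the four parts of the primary objective therefore gives no information on variability itself.

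Two things add to this. First, the reader cannot tell which SDs the rule refers to, because the same measures are called primary in one place and secondary in others. Second, the SD is meant to feed the RCT size, and an SD from ten children is imprecise. Without a rule for that imprecision, the plan leaves open whether the RCT will be sized on a value that may well be too low.

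**Working it through.** The protocol article gives no SD, target difference, power or RCT size, so there is no figure of its own to reproduce.

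**Can the criterion fail?** The four rules side by side:

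| Criterion | Threshold | Result that fails it |
|---|---|---|
| Recruitment | 70% | consent below 70% |
| Retention | 80% | completion below 80% |
| Adherence | 20 min per day | mean use below 20 min |
| Variability | none | no SD value; only too few usable data to compute one |

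**Which outcomes?** Table 1 grades COP sway area, COP velocity and RMS of COP sway as Primary for static balance, and the same three for the five-times-sit-to-stand test (5TSTS): 3 + 3 = 6 entries. Assessment protocols then has static stance tested with eyes open and closed, on a firm and on an unstable surface, with tandem stance attempted. Table 1 does not say which condition supplies the static value.

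**How precise is the SD?** Inputs: n = 10, so 9 degrees of freedom. Assumption not in the documents: normally distributed outcome. The 95% limits are s × √(9/χ²), with the 97.5% and 2.5% points of χ² on 9 degrees of freedom, 19.02 and 2.70:

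- Lower: √(9/19.02) = 0.688
- Upper: √(9/2.70) = 1.826

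For a comparison of two means at a fixed difference, n is proportional to SD². The n multipliers are 9/19.02 = 0.473 and 9/2.70 = 3.333. From limit to limit this is 19.02/2.70 = 7.04-fold. The span is 5.1-fold at 90% confidence and 3.5-fold at 80%. With eight analysable children (80% of ten) it is 9.5-fold at 95%.

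**In children per arm.** Assumptions not in the documents: two-sided alpha 0.05, 80% power, 1:1 allocation, n per arm = 2 × (1.960 + 0.842)² × SD²/difference². With the difference expressed in pilot SDs:

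| Difference | At lower limit | At point SD | At upper limit |
|---|---|---|---|
| 0.3 SD | 83 | 175 | 582 |
| 0.5 SD | 30 | 63 | 210 |
| 0.8 SD | 12 | 25 | 82 |

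**If the point SD alone were used.** The sample SD falls below the true SD with probability P(χ² on 9 df < 9) = 0.56. True power is Φ(2.802 × s/σ − 1.960), with s the pilot SD and σ the true SD. Averaged over the sampling distribution of s, this is 74%. Power is below 70% when s/σ < (1.960 + 0.524)/2.802 = 0.887, that is, when χ² < 9 × 0.786 = 7.08, which has probability 0.37.

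**If a one-sided 80% upper limit were used.** The 20% point of χ² on 9 degrees of freedom is 5.38. The SD multiplier is √(9/5.38) = 1.293 and the n multiplier is 9/5.38 = 1.67. Mean true power becomes about 88.5%, and the chance of power below 70% is P(χ² < 7.08/1.67 = 4.23), about 0.10.

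**The case against.** The strongest reply is that this is an openly exploratory pilot. It does no hypothesis testing and disclaims efficacy, and wide uncertainty is a property of any ten-child sample. That is right as far as it goes: the sample size is not the fault. But feasibility is the declared primary aim, and the rule stands in the article beside three quantified ones, so it can be judged as written.

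A second reply is that Statistical treatment promises confidence intervals to guide the RCT size. This is a real but partial mitigation. The sentence does not say that the interval is for the SD, that an upper limit will be used, or that either bears on the progression decision. Because of it, however, one cannot say that the pilot will hand over an undersized RCT; the power figures hold only if the point SD is used alone.

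Three stronger readings are tempting and are not supported:

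- *Every possible dataset passes.* The rule would fail if too few children gave usable data. The Discussion expects some difficulty with skin markers, and tandem stance is only to be attempted. That failure would concern completion, not variability.
- *The team will choose the outcome with the smallest SD or the largest effect size.* The documents say only that the results will inform outcome selection and that effect sizes will be reported. The candidates are also in different units, so their SDs cannot be ranked directly.
- *There are 18 competing primary measures.* That count multiplies three static variables by five stance conditions and adds three for the 5TSTS. Table 1 lists six Primary entries, and the plain reading of the criterion's label points to those.

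**Conclusion.** The point holds. As a test of variability the fourth criterion does not discriminate, because no SD value fails it, and the outcomes it covers are labelled inconsistently. Both are faults in a stated decision rule and do not depend on any calculation.

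The calculation shows why the missing bound matters. At n = 10 and under normality, the RCT size implied by the two 95% limits of the SD runs from 0.47 to 3.33 times the point value. The seven-fold figure is limit to limit; against the point estimate the upper limit is 3.33 times. The mean power of 74% and the 37% chance of power below 70% rest further on a two-sided 5% test, a correct target difference, and planning on the point SD alone, which the documents neither state nor exclude. Fewer analysable children would widen the range.

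**What to change.** Before data are seen:

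1. Name the outcome and test condition whose SD will size the RCT, or a short named set drawn from the six COP entries that Table 1 grades Primary. A short set is compatible with the objective of informing outcome selection.
2. Make the labels agree across the criterion, the secondary objective and Table 1.
3. Restate the criterion: met if the RCT n per arm, computed from an upper confidence limit of the named SD at a stated worthwhile difference and 80% power, is no more than a stated recruitable maximum. A one-sided 80% limit is one reasonable convention.
4. State in Statistical treatment that the confidence interval meant is the one for this SD, and that its upper limit feeds the criterion.

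No new data are needed. The cost is more than rewording: the team must commit to a worthwhile difference and a maximum RCT size, neither of which the documents now give. With the one-sided 80% limit the planned RCT is 1.67 times as large as on the point SD; at a difference of 0.5 pilot SD, that is about 63 × 1.67 = 105 per arm instead of 63.
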